## Abstract

**Background/Objectives**: Anxiety disorders are highly prevalent and impairing psychiatric conditions. Conventional diagnostic approaches based on symptom checklists lack biological specificity and often fail to guide treatment decisions effectively. This study protocol outlines a multidimensional, prospective investigation designed to identify behavioral and neurobiological biomarkers predictive of treatment response in individuals with anxiety-related symptoms, grounded in the Research Domain Criteria framework. **Methods**: This observational, longitudinal study (NCT06773585) will include a transdiagnostic sample of clinical anxiety group alongside a healthy control group (185 participants, including 145 patients with anxiety disorders and 40 healthy controls). Participants will undergo comprehensive baseline assessments, including clinical interviews, self-report questionnaires, a virtual reality (VR)-based behavioral task, electroencephalography (EEG), electrocardiography (ECG), and structural and functional brain magnetic resonance imaging. Follow-up assessments will be conducted at 2, 6, and 12 months, with recruitment and data collection planned from 2024 to 2029. These complementary modalities are integrated to capture behavioral, physiological, and neural indicators of anxiety and its treatment response. Multimodal baseline features will be used to construct machine-learning models predicting treatment response, defined as ≥40% reduction in anxiety severity scores. Longitudinal analyses will examine symptom trajectories and neural mechanisms associated with response. Neurobiological comparisons will be made across timepoints and between responders, non-responders, and healthy controls. **Conclusions**: By identifying objective, biologically grounded markers of anxiety and treatment response, our findings will contribute to the development of personalized assessment tools and scalable digital interventions for psychiatric care.

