The primary objective of this study is to delineate neurobehavioral biomarkers associated with treatment response in individuals with anxiety-related disorders using a transdiagnostic approach. Specifically, the present study aims to delineate patterns of neural and behavioral markers that cut across diagnostic boundaries—including panic disorder, SAD, GAD, agoraphobia, and specific phobia—thereby capturing shared pathophysiological processes relevant to therapeutic responsiveness. Healthy controls are included as a reference group to distinguish disorder-related changes from normative variability. We hypothesized that multimodal integration of VR, EEG, 3D skeletal tracking, and neuroimaging data will enable a more mechanistic and predictive understanding of anxiety and its treatment response beyond categorical diagnoses.

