### 2.7. Sample Size and Power Considerations

This study is designed to identify predictive biomarkers of treatment response through multimodal data modeling in a prospective, observational framework. Since the primary goal is to develop prediction models rather than to test predefined hypotheses, traditional power calculations based on inferential statistics are not directly applicable.

For the cross-sectional comparison between the clinical anxiety group and the healthy control group, a medium effect size (Cohen’s d = 0.5) was assumed based on prior neuroimaging meta-analyses [32]. This yielded a minimum required sample size of 36 participants per group to achieve 80% power at a two-sided α = 0.05. Accounting for a 10% attrition rate, the control group target was set at 40 participants.

Sample size planning for predictive modeling was based on guidelines by Riley et al. [33], which recommend ensuring a sufficient number of events per predictor parameter to reduce the risk of model overfitting. Although the dataset includes numerous raw variables across clinical, behavioral, physiological, and neuroimaging domains, only a subset (~20 variables) will be used in each model following feature selection procedures. Assuming a non-response rate of 25% (the reported remission rate of 38–75% at 6 months) [34,35], at least 80 non-responders would be required to ensure four events per predictor. Accordingly, the clinical anxiety group was targeted at 145 participants to allow for a 20% dropout rate and ensure sufficient statistical power for model development.

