### 3.2. Brain MRI Analysis

Preprocessing for MRI data will use standardized pipelines: fMRIPrep v24.0 for T1 and resting-state fMRI (anatomical segmentation, motion correction, spatial normalization, and smoothing at 6 mm full-width half maximum), and QSIPrep v0.21 for DWI (eddy-current correction, bias-field correction, and tensor fitting).

Structural MRI, diffusion-weighted imaging (DWI), and resting-state fMRI will be analyzed to comprehensively characterize brain structure, white matter integrity, and intrinsic functional organization associated with anxiety and treatment response. Structural MRI will yield cortical thickness and gray matter volume measures; DWI will provide white matter microstructural indices, including fractional anisotropy and mean diffusivity; and resting-state fMRI will be used to derive functional connectivity, amplitude of low-frequency fluctuations, and regional homogeneity as candidate neurobiological features for group comparisons and predictive modeling.

Group-level comparisons will be performed between (i) healthy controls and anxiety participants and (ii) responders and non-responders using general linear models with age and sex as covariates. Multiple comparisons will be adjusted using the false discovery rate. Significant neural indices will be further examined as candidate predictive features in multimodal modeling.

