### 3.3. Predictive Modeling of Treatment Response

The primary objective is to develop machine-learning models that predict treatment response (≥40% PDSS reduction at 2, 6, and 12 months). Binary (responder vs. non-responder) and three-group models (healthy control, responder, non-responder) will be evaluated. Predictor features will include sociodemographic and psychiatric-history variables, clinical and psychometric scores, VR-derived behavioral indices, EEG/ECG features, 3D skeletal tracing, and neuroimaging markers. In most models, age and sex will be treated as basic covariates given their known influence on neural and behavioral measures. Lifestyle variables (e.g., education, smoking, alcohol use) and treatment-related clinical variables (medication use and psychotherapy) will be systematically recorded and incorporated either as covariates to adjust for treatment effects or as candidate predictive features, depending on the specific modeling objective and analytic context.

Predictor inclusion and feature reduction will be guided by a combination of theoretical relevance and empirical criteria. Candidate variables will undergo an initial screening based on prior literature and clinical interpretability. Dimensionality will then be reduced using data-driven feature-selection procedures, such as penalized regression methods (e.g., LASSO) or feature-importance-based ranking, with the number of retained features determined by model performance and stability rather than a predefined target. Variables exhibiting substantial multicollinearity (e.g., variance inflation factor > 5), redundancy, or consistently low contribution across cross-validation folds may be excluded prior to model fitting.

All features will be standardized, and missing values handled using multiple imputations by chained equations or similar robust approaches. Depending on data characteristics, dimensionality-reduction techniques (e.g., principal component analysis) may be applied before model fitting.

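### The abstract names responders, non-responders and controls as the neurobiological comparison groups, but Section 3.2 lists no test of either response class against controls, and its pooled patient contrast dilutes an abnormality confined to one class

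*Protocol article*

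**What the plan says.** The Abstract announces: "Neurobiological comparisons will be made across timepoints and between responders, non-responders, and healthy controls". (The part about timepoints is not taken up here.) The Introduction gives the controls their purpose: "Healthy controls are included as a reference group to distinguish disorder-related changes from normative variability".

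Section 3.2, on brain MRI, sets out the group tests: "Group-level comparisons will be performed between (i) healthy controls and anxiety participants and (ii) responders and non-responders using general linear models". Both contrasts are adjusted for age and sex. The section continues: "Multiple comparisons will be adjusted using the false discovery rate", and then: "Significant neural indices will be further examined as candidate predictive features in multimodal modeling".

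Controls and the two response classes appear together only in Section 3.3, where "three-group models (healthy control, responder, non-responder) will be evaluated". These are prediction models, judged by area under the curve, F1 score and balanced accuracy.

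Section 2.7 sizes the control group for the comparison of all patients with controls, for which "a medium effect size (Cohen’s d = 0.5) was assumed based on prior neuroimaging meta-analyses". Section 2.6 defines response at 2, 6 and 12 months. Section 3.4 labels all analyses exploratory.

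**The concern.** Three groups are named in the Abstract, yet the two listed contrasts use the controls only once, against all patients as a single group. That contrast is a mean of the responder–control and non-responder–control differences, weighted by class size. If an index is abnormal in one class only, the other class pulls the pooled difference towards zero. If the classes deviate in opposite directions, the differences partly cancel.

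The responder–non-responder contrast may still find the index. The reader then knows that the classes differ, but no listed test says whether non-responders, responders or both depart from normal. For a marker of treatment response, that is a natural use of a healthy reference group. A non-significant pooled result beside a significant class difference invites the conclusion that the marker lies within normal variation, and the pooled test has little power to support that.

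**Working it through.** **Inputs from Section 2.7.** 145 patients with 20% dropout: 145 × 0.80 = 116. Non-response 25%: 116 × 0.25 = 29 non-responders and 87 responders. Controls: 40, or 40 × 0.90 = 36 after the stated 10% attrition. Effect size d = 0.5, two-sided α = 0.05.

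**The plan's own figure.** Section 2.7 gives 36 per group for d = 0.5 at 80% power. A two-sided two-sample t-test needs 64 per group, and 36 per group gives 55%. That is a separate matter. Nothing below uses the 36-per-group claim, only the control numbers that result. The inflation steps do reproduce: 36 / 0.90 = 40 and 116 / 0.80 = 145.

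**Dilution.** With p the non-responder share, pooled d = p × d(non-responder v control) + (1 − p) × d(responder v control).
- Non-responders only, d = 0.5, p = 0.25: 0.25 × 0.5 = 0.125.
- Non-responders only, d = 0.8 (assumed, to show the range), p = 0.25: 0.25 × 0.8 = 0.20.
- Responders only, d = 0.5, p = 0.25: 0.75 × 0.5 = 0.375.

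**Power.** Noncentral t with noncentrality δ = d / √(1/n₁ + 1/n₂) and n₁ + n₂ − 2 degrees of freedom. Equal SDs, no false-discovery adjustment. Ranges run from 36 to 40 controls.

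| Scenario | Pooled patients v controls | Affected class v controls | Responders v non-responders |
|---|---|---|---|
| Non-responders only, d = 0.5, 25% non-response | δ = 0.66–0.68, 10% | δ = 2.00–2.05, 51–52% | δ = 2.33, 64% |
| Non-responders only, d = 0.8, 25% non-response | δ = 1.05–1.09, 18–19% | δ = 3.21–3.28, 88–90% | δ = 3.73, 96% |
| Non-responders only, d = 0.5, 62% non-response | δ = 1.63–1.69, 37–39% | δ = 2.45–2.54, 68–71% | δ = 2.61, 74% |
| Responders only, d = 0.5, 25% non-response | δ = 1.97–2.05, 50–53% | δ = 2.52–2.62, 71–74% | δ = 2.33, 64% |

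The 62% row takes the low end of the remission range in Section 2.7 as a response rate (1 − 0.38). It gives 116 × 0.62 ≈ 72 non-responders and a pooled d of 0.5 × 72/116 = 0.31.

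**Joint result.** A simulation (10,000 runs, 36 controls, 87 responders, 29 non-responders, abnormality in non-responders only) shows how often the pooled test is non-significant while responders and non-responders differ significantly: about 59% of runs at d = 0.5 and about 82% at d = 0.8. At d = 0.5 both tests missed the marker in about 32%. Pooled power in the simulation is slightly lower than in the table (9% and 16%), because mixing two classes with different means widens the patient variance.

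**The case against.** The strongest reply is that the Abstract names three groups without promising every pairwise test. The two contrasts between them involve all three groups, and Section 3.3 adds three-group models with imaging features. Section 3.2 covers MRI only. Section 3.3 and the Figure 3 caption also mention neurobiological profiling whose detail is not visible, and an article may leave a full list of exploratory contrasts to a fuller document. This stands against any charge of contradiction. It does not remove the gap: Section 3.2 does enumerate its contrasts, and a classifier does not estimate an adjusted class-against-control difference for a neural index.

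A reader might infer that the study will call such a marker normal variation. The document states no such rule. Section 3.2 carries significant indices forward without requiring significance against controls, so a marker found by the responder contrast is kept. The figures show how often the pooled test is non-significant, not how often anyone misreads it.

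A reader might also infer that controls were enrolled to show which class is abnormal. Section 2.7 sizes them for the pooled comparison, and the Introduction speaks of disorder-related change in general.

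Nor is the position of each class wholly lost. Non-responder minus control equals the pooled difference plus the responder share times (non-responder minus responder). Point estimates are therefore roughly recoverable if the same patients enter both contrasts. What is missing is a named test and its interval.

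Finally, at d = 0.5 the direct non-responder contrast would itself miss the marker about half the time.

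**Conclusion.** The point holds as a gap between what the Abstract announces and what Section 3.2 lists. An abnormality confined to one response class can be detected as response-related while the only listed control comparison has little chance of showing it. At the plan's d = 0.5 and 25% non-response, that comparison has about 10% power, against 51–52% for a direct one. The loss shrinks as non-response rises (37–39% against 68–71% at 62%), and is smaller when responders are the abnormal class (50–53% against 71–74%).

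These figures assume equal SDs, effects wholly confined to one class, 116 classified patients and unadjusted α. False-discovery control would lower all of them. The effect sizes within a class are assumptions: the plan gives d = 0.5 only for patients as a whole.

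This concerns a secondary, exploratory analysis. The primary prediction objective is unaffected, and a claim that the plan contradicts itself or commits to a wrong interpretation would go too far.

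**What to change.** In Section 3.2, fit one general linear model per neural index with a three-level factor (control, responder, non-responder) and the covariates already stated. Define response class at one named follow-up visit, with the other visits as sensitivity analyses, because Section 2.6 allows three. Report responder–control, non-responder–control and responder–non-responder differences with confidence intervals, keep the pooled patient–control contrast, and apply the false discovery rate across the whole family. Add one sentence saying that a response marker will not be described as normative on the strength of a non-significant pooled contrast.

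The cost is a rewritten paragraph, the choice of a visit, and two more contrasts per index, with no new data. The drawbacks are a slightly larger false-discovery family and limited power for the non-responder–control contrast at d = 0.5, so the interval should be read along with the test.

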## 1. Introduction

Anxiety disorders are among the most prevalent and disabling psychiatric conditions, affecting psychological functioning, interpersonal relationships, and overall life satisfaction worldwide [1]. Recent epidemiological trends indicate a global rise in the incidence of anxiety disorders, paralleled by increasing healthcare costs and socioeconomic burdens [2]. Despite their high prevalence, anxiety disorders remain biologically elusive.

Recent large-scale genome-wide association studies have revealed a highly polygenic architecture underlying anxiety and related affective traits, identifying numerous genome-wide significant loci across international biobank and consortium datasets [3,4,5]. However, the proportion of variance explained by individual variants remains small, and mechanistically interpretable or pharmacologically actionable targets are still scarce. These findings highlight the need to integrate genomic insights with multimodal neurobehavioral data to elucidate how genetic risk translates into clinical expression and therapeutic responsiveness [3]. Furthermore, treatment outcomes remain difficult to predict, as current diagnostic systems provide limited guidance in identifying individuals likely to benefit from specific interventions [6,7]. These challenges underscore the need for a more biologically grounded, individualized approach to the assessment and management of anxiety.

Traditional psychiatric classification systems, such as the Diagnostic and Statistical Manual of Mental Disorders (DSM), rely primarily on symptom-based categories and clinical interviews. These approaches, while valuable for diagnostic consensus, are inherently limited by subjectivity, poor inter-rater reliability, and a lack of neurobiological specificity [8,9]. The categorical nature of DSM-based diagnoses obscures underlying heterogeneity and contributes to substantial overlap across disorders, thereby hindering biomarker discovery and the development of precision-guided treatments [10].

In response to these limitations, the US National Institute of Mental Health proposed the Research Domain Criteria (RDoC) framework as an alternative dimensional model of psychopathology. RDoC promotes the integration of data across multiple units of analysis—including genetics, circuits, behavior, and self-report—within transdiagnostic constructs. Within this framework, anxiety is conceptualized primarily under the Negative Valence Systems domain, particularly the “Potential Threat” construct [11].

The RDoC approach has demonstrated substantial empirical progress. Large-scale initiatives and meta-analytic efforts have established reproducible neural and behavioral constructs across affective and anxiety spectra [12,13]. For instance, recent RDoC-aligned neuroimaging and electrophysiological studies showed a shared threat-anticipation circuit involving the central extended amygdala, periaqueductal gray, and prefrontal cortex that is dynamically engaged during certain and uncertain threat [14]. Building on this foundational understanding of threat processing circuitry, subsequent studies have mapped dysregulation within this frontal-limbic network to heightened threat processing and impaired emotion regulation across generalized anxiety disorder (GAD) and post-traumatic stress disorder [15]. These advances illustrate how integrating neural-circuit, behavioral, and self-report measures under transdiagnostic constructs can reveal common mechanisms underlying anxiety-related phenomena [16,17,18]. These findings suggest that brain circuits involved in threat detection and regulation may serve as transdiagnostic, mechanistic biomarkers of anxiety. Nevertheless, although some longitudinal and multimodal studies have examined neurobiological correlations of anxiety, relatively few have focused on prospective prediction of treatment response using integrated VR-based behavioral and neurobiological assessments within an RDoC-aligned framework. To address this gap, we proposed a longitudinal, multimodal approach—combining virtual reality (VR), electroencephalography (EEG), and magnetic resonance imaging (MRI)—to address the gap by offering a more comprehensive, predictive model of anxiety.

Empirical evidence from individual modalities has also advanced our understanding of anxiety-related processes. EEG studies have identified abnormal theta and beta band activity and altered error-related negativity during anticipatory and conflict processing in anxiety [19,20]. Electrocardiography (ECG) has consistently shown reduced heart-rate variability and increased sympathetic tone, reflecting heightened physiological arousal and impaired stress regulation [21,22]. Neuroimaging studies further demonstrate hyperactivation of the amygdala, insula, and prefrontal regions, along with disrupted connectivity within the default mode and salience networks in anxiety disorders [23,24].

VR offers a promising platform for implementing RDoC-informed assessments by enabling standardized, ecologically valid exposure to anxiety-provoking stimuli [25]. VR environments can be integrated with real-time biosignal monitoring—including EEG, ECG, and 3D skeletal tracking—to capture multimodal, task-evoked responses [26]. This capacity allows for the measurement of behavioral, physiological, and neural responses within a controlled but naturalistic context. Conceptually, this multimodal assessment approach maps directly onto RDoC domains such as Negative Valence and Arousal/Regulatory Systems and offers scalability, reproducibility, and objectivity that are difficult to achieve with traditional self-report methods.

Considering these opportunities, we developed a prospective observational study aimed at identifying neurobehavioral biomarkers of anxiety and predicting treatment response. Although participants are recruited based on DSM-5 diagnoses of anxiety disorders—including panic disorder, social anxiety disorder (SAD), GAD, agoraphobia, and specific phobia—the analytic focus is on dimensional variations in anxiety symptoms that cut across diagnostic boundaries. This transdiagnostic strategy acknowledges that current categorical systems provide limited information about therapeutic responsiveness and seeks to characterize symptom-level mechanisms that underlie anxiety across disorders. The study integrates VR-based behavioral tasks, physiological monitoring, and multimodal neuroimaging within an RDoC-aligned conceptual framework. By combining these multimodal data with conventional clinical assessments, it aims to contribute to the development of biologically informed, scalable tools for personalized psychiatric care.

The primary objective of this study is to delineate neurobehavioral biomarkers associated with treatment response in individuals with anxiety-related disorders using a transdiagnostic approach. Specifically, the present study aims to delineate patterns of neural and behavioral markers that cut across diagnostic boundaries—including panic disorder, SAD, GAD, agoraphobia, and specific phobia—thereby capturing shared pathophysiological processes relevant to therapeutic responsiveness. Healthy controls are included as a reference group to distinguish disorder-related changes from normative variability. We hypothesized that multimodal integration of VR, EEG, 3D skeletal tracking, and neuroimaging data will enable a more mechanistic and predictive understanding of anxiety and its treatment response beyond categorical diagnoses.

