The full multimodal analytic workflow supporting these predictive models is summarized in Figure 3. This figure outlines the end-to-end structure of the pipeline, beginning with modality-specific preprocessing (sociodemographic/clinical variables, VR behavioral data, EEG/ECG signals, 3D-skeletal tracking, and MRI), followed by a multimodal feature-integration stage, and culminating in supervised-learning models and validation procedures. This framework visually captures how heterogeneous data streams are harmonized into a unified dataset for treatment-response prediction and how complementary neurobiological profiling analyses interface with the main machine-learning pipeline.

Various supervised-learning algorithms—such as logistic regression, support-vector machines, random forests, or gradient-boosting methods (e.g., XGBoost, CatBoost)—may be compared. Model performance will typically be evaluated through k-fold or nested cross-validation, using metrics such as area under the curve, F1 score, and balanced accuracy. Model interpretability will be explored through feature-importance or SHapley Additive exPlanations-value analyses. All analytic pipelines will be version-controlled to ensure reproducibility.

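### The hypothesis that multimodal integration predicts response better than categorical diagnosis has no model comparison behind it; Section 3.3 varies only outcome coding and algorithm on one pooled feature set

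*Protocol article*

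**What the plan says.** The hypothesis stands at the end of the Introduction: "We hypothesized that multimodal integration of VR, EEG, 3D skeletal tracking, and neuroimaging data will enable a more mechanistic and predictive understanding". The sentence goes on to name what integration should improve on: "predictive understanding of anxiety and its treatment response beyond categorical diagnoses". It therefore has a mechanistic half and a predictive half, and its stated comparator is categorical diagnosis.

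Section 3.3 describes the prediction models.

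- **Candidate predictors:** "Predictor features will include sociodemographic and psychiatric-history variables, clinical and psychometric scores, VR-derived behavioral indices, EEG/ECG features, 3D skeletal tracing, and neuroimaging markers".
- **Integration:** the workflow shows how "heterogeneous data streams are harmonized into a unified dataset for treatment-response prediction".
- **Outcome coding:** "Binary (responder vs. non-responder) and three-group models (healthy control, responder, non-responder) will be evaluated".
- **Algorithm:** "Various supervised-learning algorithms—such as logistic regression, support-vector machines, random forests, or gradient-boosting methods (e.g., XGBoost, CatBoost)—may be compared".
- **Attribution to features:** "Model interpretability will be explored through feature-importance or SHapley Additive exPlanations-value analyses".

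Section 2.7 explains why conventional power calculations are not used: "Since the primary goal is to develop prediction models rather than to test predefined hypotheses". Section 3.4 calls all analyses exploratory.

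**The concern.** A statement that one approach predicts better needs a model with it and a model without it, judged on the same patients. Section 3.3 names two contrasts, outcome coding and algorithm. Neither removes a modality or falls back to diagnosis.

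Suppose the plan is followed and the combined model reaches some cross-validated AUC. That figure does not show whether diagnosis and routine clinical variables would have done as well, or whether one modality would have been enough. The study aims at scalable tools, and its work-up includes an MRI scan of about 40 minutes and a VR session with EEG and ECG. Whether these components add prediction is a practical question, and the plan leaves it open.

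**Working it through.** The protocol gives no figure to reproduce here. The check has three parts.

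**1. Hypothesis against planned contrasts**

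| Contrast | Where | Planned? |
|---|---|---|
| Binary vs three-group outcome | 3.3 | Yes |
| Between algorithms | 3.3 | Optional |
| Combined vs diagnosis-only or clinical-only | – | Not stated |
| Combined vs one modality, or one left out | – | Not stated |
| Group comparisons of MRI indices (controls vs patients, responders vs non-responders) | 3.2 | Yes, but these are not competing prediction models |

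The EEG and MRI direct profiling in the Figure 3 legend is described as running parallel to prediction, not as a rival model. Section 3.2 partly serves the mechanistic half of the hypothesis. Nothing serves the predictive half.

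**2. Can importance values stand in for the comparison?**

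Assumed set-up: modality A drives response, and modality B is correlated with A but adds no information. Training uses n = 145 × 0.8 = 116 completers, and AUC is measured on 4,000 new patients. Importance is the share of absolute standardised coefficients.

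One feature per modality, ridge logistic regression, 400 runs, VIF = 1/(1 − ρ²):

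| ρ | VIF | Share given to B | Change in AUC on adding B |
|---|---|---|---|
| 0.50 | 1.3 | 21% | −0.008 |
| 0.70 | 2.0 | 27% | −0.007 |
| 0.85 | 3.6 | 34% | −0.005 |
| 0.89 | 4.8 | 38% | −0.005 |

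All four VIFs pass the example screen of VIF above 5 in Section 3.3.

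With five features per modality, B being A plus noise of SD 0.7, and 200 runs with assumed effect sizes:

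- **Ridge:** B received 37–40% of importance, and AUC changed by about −0.01.
- **LASSO:** B received 27–31%, and AUC changed by −0.004 to −0.007.

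The share depends on the correlation and the penalty. In every setting it is sizeable and there is no gain in AUC.

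**3. How precise would the missing comparison be?**

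Section 2.7 assumes 25% non-response. This gives 116 × 0.25 = 29 non-responders and 87 responders. The AUCs and the correlation r between the two AUC estimates are assumptions. The Hanley–McNeil variance of one AUC A is

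[A(1−A) + (m−1)(Q1−A²) + (n−1)(Q2−A²)]/(mn), with Q1 = A/(2−A) and Q2 = 2A²/(1+A).

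For m = 29 and n = 87:

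- A = 0.70: (0.21 + 28 × 0.0485 + 86 × 0.0865)/2523 = 0.00357, so SE = 0.060.
- A = 0.75: (0.1875 + 28 × 0.0375 + 86 × 0.0804)/2523 = 0.00323, so SE = 0.057.

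SE of the paired difference = √(SE₁² + SE₂² − 2r·SE₁·SE₂):

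| r | SE | 95% half-width (1.96 × SE) |
|---|---|---|
| 0.3 | 0.069 | 0.14 |
| 0.5 | 0.058 | 0.11 |
| 0.7 | 0.045 | 0.09 |

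Over AUC pairs from 0.65 vs 0.70 to 0.70 vs 0.80, the SE runs from 0.044 to 0.072. Two-sided 5% power is 10–20% for a gain of 0.05 and 30–62% for a gain of 0.10. A binormal simulation with within-class score correlation of 0.3–0.7 gave SEs of 0.044–0.067, a half-width of 0.09–0.13.

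The other end of the quoted remission range (38%) would give 116 × 0.62 ≈ 72 non-responders. Power is then 13–28% and 42–81%.

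These SEs treat the model scores as fixed, so refitting across folds would add variability.

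**The case against.** **The study is exploratory.** Section 2.7 says model development takes precedence over testing predefined hypotheses, and Section 3.4 labels everything hypothesis-generating. A reader might infer that Section 2.7 flatly contradicts the Introduction. It does not: the sentence explains why conventional power calculations are not directly applicable, and an expectation stated in an introduction can sit beside it. What remains is that an exploratory study can still estimate a difference, and this one plans no such estimate.

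**SHAP is planned only for interpretability.** This is correct. A reader might infer that the protocol means to use SHAP values as proof that a modality adds value, or that it would recommend the full work-up on that basis. The text says neither. The narrower point stands: no other planned output attributes prediction to modalities, and this one cannot show added value.

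**The comparator is diagnosis, not the best single modality.** This also stands, and it sets the priority of the fix. A reader might take the hypothesis to be only that many modalities beat one. As worded, its nearest benchmark is a diagnosis-only or clinical-only model, with modality contrasts informing the integration part. Neither is planned.

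**An article condenses, and Section 3.3 is permissive.** It speaks of several models and uses terms such as may and typically, so reduced models are not ruled out and an unseen analysis plan could add them. But Section 3.3 lists its contrasts in some detail, and the one that the hypothesis needs is not among them.

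**The importance share depends on the set-up.** Ridge spreads weight over correlated features, and the protocol's named example is LASSO with optional removal of redundant variables. LASSO lowers the share but does not remove it. The simulation shows a general property of importance values, not an error in a protocol figure.

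**Conclusion.** The concern holds for the predictive half of the hypothesis. Section 3.3 as written contains no contrast that could show that integration predicts treatment response better than diagnosis, clinical variables or a single modality. The mechanistic half is partly covered by Section 3.2.

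Importance values do not close the gap: about 20–40% of importance went to a redundant modality, with no gain in AUC. That range rests on assumed correlations, effect sizes and penalties.

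The missing comparison is feasible as an estimate with an interval but not as a powered test. The half-width is about 0.09–0.14 in AUC, which rests on 25% non-response, 20% dropout, AUCs of 0.65–0.80 and correlations of 0.3–0.7. A pass/fail rule would not suit a study of this size and exploratory status.

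**What to change.** Add the following to Section 3.3.

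1. Fit (a) a diagnosis/clinical-only model, (b) models with each modality alone or left out, and (c) the combined model. Use the same algorithm and the same outer cross-validation folds, with feature selection inside the folds.
2. Report paired differences in AUC and in Brier score or log-loss with bootstrap intervals; 1,000 bootstrap iterations are already planned in Section 3.4. Combined versus diagnosis/clinical-only is the main contrast, and the modality contrasts are descriptive.
3. If a best single modality serves as comparator, repeat its selection inside the resampling. Otherwise picking the highest of several AUCs on the same data biases the contrast.
4. State that SHAP and importance values are descriptive and are not evidence of added value.
5. Either word the Introduction's hypothesis as an exploratory aim, or limit any claim of predictive gain to what these differences show.

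The cost is analysis wording and extra model fits on data already to be collected. The downside is that the intervals will be wide with about 29 non-responders, so the likely result is that a small gain can be neither shown nor excluded.
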